#### Data processing and analysis

For the process evaluation, quantitative data obtained from the participation audit, online metrics, and online survey (close-ended questions) will be analyzed using descriptive statistics, and explored using cross-tabulations to identify differences (if any) between participant groups (i.e., teachers/administrators, parents/caregivers) and between ECECs. Qualitative data obtained from the online survey and outcomes questionnaire (open-ended questions), and transcribed FGDs will be examined using thematic analysis, guided by a realist framework which assumes that language captures participants’ experiences of reality [40]. A six-phase analytic process will be adopted consisting of: familiarizing with the data, generating codes, generating initial themes, reviewing and developing themes, refining, defining, and naming themes, and writing the report [22]. Coding and theme generation will take inductive (i.e., bottom up approach) and semantic approaches (i.e., explicit meaning of gathered data) as these are known to align well with a realist framework [40]. Thematic analysis will be supported by NVivo 12.0.

Findings from the quantitative and qualitative analyses will be converged, guided by the RE-AIM framework [25] to answer the evaluation questions (see Table 1). The converged analysis will account for participant groups and individual ECECs, accounting for differences in the background and volume of engagement during the implementation.

For the outcome evaluation, the proportions of children who meet the guidelines will be measured based on the parent-proxy questionnaire and accelerometer monitoring. A minimum of 4 days of accelerometer data will be required to be considered valid [39]; cut-points developed by Evenson et al. [41] and Pate et al. [42] have been recommended to determine time spent in physical activity and sedentary behavior in young children [37]. Meeting the guidelines is defined as ≥180 min/day of total physical activity (of which 60 min is vigorous physical activity), ≤1 h/day of sedentary screen time, and 10–13 h of sleep per 24-h period [4]. Logistic regression will be conducted to determine the contribution of the dissemination activities (i.e., implementation or comparison group), child characteristics, and ECEC on the likelihood of a child meeting each guideline component (i.e., primary outcome).

The secondary outcome of knowledge and awareness of the movement guidelines by parents and teachers will be compared between the implementation and comparison groups using descriptive and inferential statistics, whilst accounting for participant characteristics (e.g., age, sex) and ECEC. Parametric statistics will be used when assumptions of normality are met. All statistical analysis procedures will be performed on SPSS 26.0 with statistical significance set at *p* < 0.05.

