#### Recruitment

Eight ECECs, from across the three major districts of Hong Kong (i.e., Hong Kong Island, Kowloon, New Territories), will be recruited to join the implementation. The inclusion criteria for ECECs are that they: (1) are included in the published list of kindergartens by the Education Bureau, (2) follow the *Kindergarten Education Curriculum Guide of Hong Kong* [23], and (3) offer classes across three kindergarten levels (i.e., K1, K2, K3). A second group of eight ECECs, who meet the same eligibility criteria and with comparable background to the first group (i.e., ECEC size, location), will also be recruited to join a comparison group for the outcome evaluation. This second group will participate in the activities for the dissemination of the movement guidelines (i.e., educational meetings, social media, resource materials) in the school year following the implementation period. Given the constraints associated with the recruitment of ECECs to participate in projects during a pandemic, the recruitment process will be purposive. The timeline for joining the project will be the prerogative of each ECEC (i.e., hence, the group to which they will be allocated to).

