#### Summative outcome evaluation

A non-randomized observational study design will be used for the outcome evaluation, where outcomes will be compared between the implementation group and the comparison group. The implementation group will consist of teachers and parents from the ECECs that participated in the dissemination activities; the comparison group will consist of teachers and parents from a matched group of ECECs who have yet to join the implementation. ECECs in the comparison group will join educational meetings and receive all materials in the subsequent school year after the implementation period. The primary outcome of interest is the extent to which children in the ECEC groups meet the guidelines for physical activity, sedentary screen time, and sleep. The secondary outcomes are the knowledge and awareness of healthy movement guidelines by teachers and parents.

Teachers and parents will be invited to respond to online surveys at two additional time points: immediately following the implementation period (Time 3, T3), and 4 months post-implementation (Time 4, T4). These surveys will measure the secondary outcome by assessing the participants’ knowledge and awareness of the movement guidelines. The surveys for parents will include additional questions to measure the primary outcome by assessing the extent to which children meet the guidelines through a parent-proxy questionnaire. The said proxy-report questionnaire is made up of items from validated English-language questionnaires [34, 35] which were translated and back-translated [36] for use among parents of young children in Hong Kong. The translated questionnaire had been found to have good internal consistency (Cronbach’s alpha = 0.762), and is currently being used in an ongoing longitudinal study of child development in Hong Kong. Finally, open-ended questions will query on family strategies that relate to children meeting the movement guidelines.

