### Ethical considerations

The study was approved by the Human Research Ethics Committee of the Education University of Hong Kong (reference number 2019–2020-0145). Participating ECECs will be recruited through their principals, who will provide written consent for their participation. Subsequently, teachers and parents will provide written consent prior to joining any data gathering procedure. Participants who do not consent to participate in the study may still join the educational meetings and use the social media platforms, but they do not have to participate in any of the data gathering procedures. The potential benefits of the dissemination plan will not be withheld from ECECs in the comparison group because they will receive the same dissemination activities following completion of the outcome evaluation. All participants will also be invited to provide written consent for their identifiable data to be held by the research team for possible future follow-up for no longer than 5 years following study completion.

The findings of this study will be disseminated in scientific conferences and peer-reviewed journals within the areas of public health and child development. Knowledge will also be shared with teachers and parents through continuous social media platforms to support more teachers and parents in enabling young children to meet the movement guidelines. Finally, insights from the implementation will be shared with the Centre for Health Protection of Hong Kong, to inform further health promotion efforts by relevant government agencies.

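### With ECEC entered as an ordinary predictor beside group, the primary logistic regression cannot estimate the group effect, because each ECEC lies wholly in one group

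*Protocol article*

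**What the plan says.** All references are to the protocol article.

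- **Primary model (Data processing and analysis).** For each guideline component, logistic regression is meant to show "the contribution of the dissemination activities (i.e., implementation or comparison group), child characteristics, and ECEC on the likelihood" that a child meets it. ECEC stands in the list on the same footing as group and child characteristics.
- **Groups (Recruitment).** The implementation group is "Eight ECECs, from across the three major districts of Hong Kong". The comparison group is "A second group of eight ECECs, who meet the same eligibility criteria and with comparable background to the first group".
- **Unit of allocation (Recruitment).** Whole ECECs choose: "The timeline for joining the project will be the prerogative of each ECEC (i.e., hence, the group to which they will be allocated to".
- **No crossover (Ethical considerations).** Of the comparison ECECs: "they will receive the same dissemination activities following completion of the outcome evaluation".
- **Outcome times (Summative outcome evaluation, Table 3).** The proxy questionnaire on the primary outcome is given "immediately following the implementation period (Time 3, T3), and 4 months post-implementation (Time 4, T4"; accelerometers are worn at T3 only. There is no measurement before implementation.
- **Secondary outcome (Data processing and analysis).** Knowledge and awareness are compared between groups "whilst accounting for participant characteristics (e.g., age, sex) and ECEC". No model is named.

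The article mentions no random effect, GEE, cluster-robust variance, ICC or design effect.

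**The concern.** Group is a property of the ECEC, not of the child. Once a single-level model has a separate term for every ECEC, those terms already explain every difference between ECECs, including the difference between the two sets of eight. Nothing is left from which to estimate a group effect. A pre-implementation measurement or a crossover of ECECs could supply a contrast within ECECs, but the outcome evaluation has neither. Having both T3 and T4 does not help, because group is constant within each ECEC at both times.

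The third stated aim is to evaluate the impact of the dissemination, and this regression is the only inferential analysis described for the primary outcome. Software may not stop with an error. It can drop a redundant column and print an odds ratio and p-value for group that compare arbitrary ECECs, so the failure could pass unnoticed into the report. An analyst who does notice may be tempted to delete ECEC, which exchanges non-estimability for standard errors that ignore clustering.

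**Working it through.** **Inputs from the article.** 8 + 8 = 16 ECECs; required total N = 242 (Participants and sample size); two-sided 5% testing is assumed, since the article gives only the 0.05 level. N = 242 is used here only to set the cluster size. It could not be reproduced for a 1:1 group comparison at OR 1.5, which needs at least 768 in total (two-sided, at a comparison-group rate near 0.45). That is a separate point, and nothing below depends on it.

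**Assumption.** The ICC, taken as 0.01 to 0.10.

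**Step 1: estimability with ECEC as a fixed factor.** Let G = 1 for implementation and D_j be the indicator of ECEC j. Because each ECEC lies in one group, G is the sum of D_j over the eight implementation ECECs. If the reference ECEC is an implementation ECEC, then equivalently G = 1 − (sum of the eight comparison indicators).

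- Columns: intercept + group + 15 ECEC indicators = 17 (checked for 16 ECECs × 15 children).
- Rank: 16.
- Rank with group deleted: still 16.

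Group therefore adds nothing to the model and has no unique coefficient. This is algebra and needs no ICC.

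**Step 2: what software could print.** One simulated data set was refitted with different redundant ECEC indicators dropped. The group odds ratio ran from 0.55 to 2.41 with the same log-likelihood (−153.737) each time. The model without ECEC gave 1.29. The data cannot choose among these fits. Depending on the order of entry, the software may instead remove group itself.

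**Step 3: if ECEC were simply removed.** Children per ECEC: m = 242/16 = 15.125. Design effect DE = 1 + (m − 1) × ICC = 1 + 14.125 × ICC. Naive SE as a fraction of the true SE = 1/√DE. True two-sided type I error = 2 × P(Z > 1.96/√DE).

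| ICC (assumed, proportion scale) | DE | Naive SE / true SE | Type I error | Effective N = 242/DE |
|---|---|---|---|---|
| 0.01 | 1.14 | 94% | 6.7% | 212 |
| 0.02 | 1.28 | 88% | 8.4% | 189 |
| 0.05 | 1.71 | 77% | 13.4% | 142 |
| 0.10 | 2.41 | 64% | 20.7% | 100 |

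**Step 4: check by simulation.** 20,000 runs per setting, 16 ECECs × 15 children, rates 0.30 and 0.50, ICC set on the latent (logit) scale. Naive logistic regression rejected a true null in 4.6–5.0% of runs at ICC 0, 7.2% at 0.02, 10.4–11.2% at 0.05 and 16.6–17.6% at 0.10. A t-test on the ECEC-level results (14 df) stayed at 4.8–5.4%.

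The simulated rates are lower than those in the table because the scales differ. At a rate of 0.30, latent ICCs of 0.05 and 0.10 are about 0.035 and 0.07 on the proportion scale. With m = 15, DE = 1 + 14 × 0.035 = 1.49 and 1 + 14 × 0.07 = 1.98, for which the formula gives about 11% and 16%. These are close to the simulated 10.4% and 16.6% at that rate.

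**The case against.** The strongest reply is that the sentence does not say fixed, indicator or ordinary. Logistic regression with ECEC among its terms could mean an ECEC random intercept, and a condensed article may leave such detail to a fuller document. It is true that non-estimability applies only to ECEC as a fixed factor; a random intercept or GEE would make the group effect estimable. But the article itself fixes the method and its terms, lists ECEC in parallel with ordinary predictors as something whose contribution is to be determined, and names no clustered method anywhere. Read as written, the terms cannot work together. If ECEC was meant as ECEC characteristics such as size or location, the model would be estimable, but the residual clustering would remain.

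Parts of the reply do stand, and they limit the point:

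- A reader might infer that the plan will report falsely narrow intervals. The article nowhere proposes to drop ECEC. The error rates in Step 3 describe a tempting repair, at assumed ICCs.
- A reader might infer that the secondary analysis fails in the same way. Its wording is looser, names no model and is compatible with a clustered analysis. It needs clarifying, but is not shown to be unworkable.
- A reader might treat the aliased coefficient as merely a low-powered test of dissemination. At OR 1.5 and a rate of 0.30 it rejects in about 15% of simulated runs at latent ICC 0.10, but it also rejects in 10.8% with no effect. Much of that is false positives from an arbitrary two-ECEC contrast, so power is the wrong word.

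**Conclusion.** The point holds for the model as stated, and it must be fixed. Entered as a fixed factor, ECEC is fully aliased with group (17 columns, rank 16), so the primary model cannot deliver the effect of dissemination. This conclusion rests only on the allocation of whole ECECs and on outcomes measured at T3 and T4 without crossover, all of which the article states.

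The warning against deleting ECEC is conditional. It needs a positive ICC, and its size (type I error of about 8%, 13% and 21% at proportion-scale ICCs of 0.02, 0.05 and 0.10) rests on assumed values and on about 15 children per ECEC. The absence of randomisation does not change this: clustering affects standard errors either way, and the article sets a significance level of p < 0.05.

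**What to change.** In Data processing and analysis, state that the primary model for each guideline component is a mixed-effects logistic regression with:

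- group, child characteristics and, sparingly, ECEC-level covariates (size, district) as fixed effects;
- ECEC as a random intercept;
- small-sample degrees of freedom that reflect 16 clusters;
- a child random effect as well, if T3 and T4 are modelled jointly.

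Report the ICC. An analysis of the 16 ECEC-level results (16 − 2 = 14 df), adjusted for child characteristics in a first stage, can serve as a sensitivity analysis. An unadjusted t-test on 16 raw proportions is not equivalent to the mixed model, because it discards child-level adjustment in a non-randomised comparison. For the secondary outcome, say that ECEC enters as the clustering term there too.

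**Cost.** The wording change is small, mixed models are available in the stated software, and the revised analysis needs no new data. The real cost is precision: intervals widen, and power falls below what a calculation for independent children implies. To keep the information of 242 independent children at the same cluster size would take 242 × DE, or about 311, 413 and 584 children at ICCs of 0.02, 0.05 and 0.10. Since cluster size is held fixed, that means more ECECs. If recruitment is closed, the loss should be stated openly.

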### Ethical considerations

The study was approved by the Human Research Ethics Committee of the Education University of Hong Kong (reference number 2019–2020-0145). Participating ECECs will be recruited through their principals, who will provide written consent for their participation. Subsequently, teachers and parents will provide written consent prior to joining any data gathering procedure. Participants who do not consent to participate in the study may still join the educational meetings and use the social media platforms, but they do not have to participate in any of the data gathering procedures. The potential benefits of the dissemination plan will not be withheld from ECECs in the comparison group because they will receive the same dissemination activities following completion of the outcome evaluation. All participants will also be invited to provide written consent for their identifiable data to be held by the research team for possible future follow-up for no longer than 5 years following study completion.

The findings of this study will be disseminated in scientific conferences and peer-reviewed journals within the areas of public health and child development. Knowledge will also be shared with teachers and parents through continuous social media platforms to support more teachers and parents in enabling young children to meet the movement guidelines. Finally, insights from the implementation will be shared with the Centre for Health Protection of Hong Kong, to inform further health promotion efforts by relevant government agencies.

### Status and timeline of the study

The study implementation commenced in September 2021. Based on the planned timeline, the implementation will continue until May 2022, and T4 data gathering is expected in September 2022.

## Discussion

The project aims to contribute towards improved health behaviors of Hong Kong young children through the enabling actions of the adults who support their development. It is believed that by targeting early childhood, the work would potentially contribute to long-term health promotion and prevention of non-communicable diseases (NCDs) as movement behaviors are known to track from childhood to adulthood [15]. Young children who engage in healthy movement behaviors are likely to become adults who will have the disposition to engage in behaviors that have protective effects against NCDs. Considering the costs that physical inactivity and highly sedentary behavior imposes on the health care system, promoting healthy movement behaviors early in childhood could contribute towards sustainable health care services. While it is outside the scope of this current project, a follow-up study could be designed to quantify the costs and benefits of investing in early childhood through actuarial models that measure the social return on investment [43].

In the short-term, the outcomes of this study directly contribute to improving the strategies of the government agencies in Hong Kong that are tasked to promote health and development among young children (i.e., health, education). The movement guidelines for pre-primary school-aged children are based on evidence that had been evaluated through robust processes [4]. By leveraging on established evidence while accounting for the local context, this project contributes to health promotion through sensible and economical utilization of resources.

### Potential challenges and mitigations

Due to the duration of the project, challenges are bound to occur. It is assumed that stakeholders would continue to be engaged over the implementation period. However, there is a risk that in the eight-month period, teachers and parents would become disengaged. To mitigate this, project staff overseeing the social media channels will ensure a continuous flow of information and feedback with the participants.

It is also acknowledged that parents in Hong Kong are known to have a bias that prioritizes academic pursuits in promoting child development [44]. Because Hong Kong parents are known to be in a position to encourage or discourage physical activity participation [45], this project will need to ensure that parents are convinced of the importance of healthy movement behaviors and the positive associations between healthy movement behaviors and academic outcomes are reiterated. Findings from the formative study which informed the dissemination plan will ensure that parents’ bias will be managed. Finally, objective (i.e., accelerometers) and subjective (i.e., questionnaire) measures of movement behaviors each have associated challenges that could impact the veracity of gathered data; the use of both approaches is meant to make up for the limitations of using them in isolation.

With the challenges mitigated, this study stands to generate findings that will inform subsequent public health promotion programs for young children in Hong Kong. The evaluation will deliver information on the uptake of the movement guidelines, the barriers and enablers that can aid uptake, and the impact of deliberately engaging teachers and parents in the promotion of healthy movement behaviors of young children. The lack of randomization for the outcome evaluation may pose as a limitation, but the combination with process evaluation will likely generate meaningful insights that will inform future implementations. While the study is contextualized to Hong Kong, the findings could be useful to other territories’ efforts of disseminating movement guidelines in young children.

## Data Availability

Data will be saved and made available subsequently through the following OSF registration: [name], [name], [name], [name], [name]. 2021. Implementation Science Approach to Disseminating Healthy Movement Guidelines for Young Children in Hong Kong. OSF. osf.io/mfut9.

## Abbreviations

CHP: Centre for Health Protection (Hong Kong)
DALY: Disability-adjusted life years
ECEC: Early childhood and education center
FGD: Focus-group discussion
NCD: Non-communicable diseases
RE-AIM: Reach, efficacy, adoption, implementation maintenance
WHO: World Health Organisation
